**Protocol Compliance**

Drug intake and adherence will be monitored by a clinical research coordinator, based on patient reports and counting of unused tablets.

| **Investigation/intervention** | **Timing (Study Day)** | **Notes** |
| --- | --- | --- |
| Informed consent | At/ before D0 | Baseline |
| Inclusion/exclusion criteria | At/before D0 | Baseline |
| Medical History | At/before D0 | Baseline |
| ECG | At/Before D0 | Baseline; for cardiologist review prior to randomisation |
| Concomitant medications | At/before D0 | Baseline; medications checked and any changes noted at each visit |
| Blood sample collected | D0 (or up to 4 wks prior) | Baseline blood sample (total 40mL): for inflammatory and immune markers as per MIA biobank protocol (32mL) plus routine preoperative bloods (FBC, EUC, LFTs*; 8mL). |
| QoL, perceived stress and state optimism scales | D0 |  |
| Nodal and/or skin metastases biopsied (2 x 2mm^2^ core biopsies for diagnosis and for tissue microarray | 28-14 days before D0 |  |
| ProCel treatment | D0 | Commenced 5d preoperatively: (D0) |
| Tumour assessment (IHC) | D6 | Excision specimens obtained after 5d of ProCel regimen and controls (D6 = day of surgery) |
| Blood sample collected | D20 (range D20-D27) | Postoperative bloods collected D20 (range D20-D27; ie 2 to 3 wks postoperatively) for inflammatory and immune markers as per MIA biobank protocol (32mL) and routine postoperative bloods (FBC, EUC, LFTs; 8mL) |
| QoL, perceived stress and state optimism scales | D20 (range D20-D27) |  |
| Adverse events | During and for 30 days after ProCel regimen | D6 (day of surgery), D20 (postop followup), D45 (30 days after ceasing medication) |
| Clinical and radiological followup | 4 months postoperatively (range 3-5 months) | Clinical review and surveillance imaging as per standard clinical practice |
| QoL, perceived stress and state optimism scales | 4 months postoperatively(range 3 – 5 months) | Performed at the time of 4 month postoperative review |

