**Study Design**

Prospective randomised controlled study; patients will be randomised to receive either the ProCel regimen perioperatively (stratified for ±systemic immunotherapy, metastatic site ie node, skin) or no ProCel regimen. For this pilot study placebo tablets will not be used and blinding is not possible for treating clinicians or participants. Investigators analysing tumour tissue and blood samples will be blinded to allocation.

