### **FBC, full blood count; EUC, electrolytes urea creatinine; LFTs, liver function tests*

**Quality of Life Questionnaires**

Participants will be asked to complete quality of life questionnaires at baseline, D20 and at 4 months post operatively.

Questionnaires to be used:

- EORTC QLQ-C30^40^
- MCQ-28^41^
- State Optimism Measure^42^
- Perceived Stress Scale^43^

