**State Optimism Measure ^42^**

***Please answer the following items based on how you feel right now, that is, at the present moment using the scale below. Try to answer each item as accurately as possible based on your response to that item alone, without regard to your answers to any previous items.***

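### The baseline questionnaires are fixed at D0 with no requirement that they precede randomisation, so in this unblinded trial they will probably be completed after the participant knows the arm

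*Protocol*

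**What the plan says.** All places are in the Protocol.

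- **First questionnaires.** The schedule table reads "QoL, perceived stress and state optimism scales | D0", with an empty notes cell. The text under Quality of Life Questionnaires says only "Participants will be asked to complete quality of life questionnaires at baseline, D20 and at 4 months post operatively".
- **Start of treatment.** The ProCel row of the table is also set at D0, with the note "Commenced 5d preoperatively: (D0". The dosing text in section 5.2 numbers the first day of both drugs as D1.
- **Other baseline items.** Consent, eligibility, medical history, ECG and concomitant medications may be done on D0 or earlier. The baseline blood sample may be taken up to four weeks before D0, and section 5.2 places it before ProCel starts. The questionnaires have neither an earlier window nor a before-treatment condition.
- **Randomisation.** It has no row and no study day. It follows the cardiologist's review: the ECG row says "Baseline; for cardiologist review prior to randomisation", and section 5.3 says the same.
- **Blinding.** The Summary (Study Design) states that "blinding is not possible for treating clinicians or participants", and there is no placebo.
- **Endpoint.** Section 3.2.3 covers quality of life, perceived stress and state optimism at 14 days and 4 months after surgery, and their correlation with blood and tumour markers.
- **Last questionnaires.** They are "Performed at the time of 4 month postoperative review". The follow-up row for that time point is "Clinical review and surveillance imaging as per standard clinical practice".

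**The concern.** A baseline score is useful because it cannot have been affected by allocation. Here the forms fall on the day on which the table also starts treatment. By then the participant must have been randomised and, in the ProCel arm, supplied with two drugs and a pulse oximeter. Nothing puts the forms ahead of those steps.

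Knowing the arm could plausibly move some of these scores. Section 1.3 suggests that β blockers may ease stress and anxiety before surgery, so participants may form expectations. The State Optimism Measure in Appendix 1 asks for answers "based on how you feel right now, that is, at the present moment".

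At stake is whether the baseline can be used for endpoint 3.2.3 at all. A pre-allocation score that was never collected cannot be recovered in the analysis. Leaving the baseline out avoids this bias but gives up the precision it would have brought, in a trial with 20 participants per arm.

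**Working it through.** The Protocol gives no figure to reproduce. It states N=40 randomised 1:1, without alpha, power, SD or effect size. The check therefore has two parts: the order of events, and an illustration of size under stated assumptions.

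**1. Order of events**

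- If drug starts on D0, as in the table, randomisation and supply happen on or before D0. The forms precede allocation only if they are done first, which is not required.
- If drug starts on D1, as in the dosing text, D0 is the day before the first dose. The table's description of surgery on D6 after five days of ProCel fits D1 to D5 (five days) rather than D0 to D5 (six days). Allocation and supply must still be done before the first dose on D1, and again nothing puts the forms first.

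On either numbering, completion after allocation is likely but not certain.

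**2. Size, under assumptions**

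From the Protocol: 20 per arm. Assumed: scores in SD units with the same SD at baseline and follow-up, two-sided alpha of 0.05, no true effect, and within-arm baseline to follow-up correlation ρ of 0.3 to 0.7. Knowing the arm shifts the D0 score in one arm by b = 0.1 to 0.5 SD and the follow-up score by c. With no true effect, the size of the spurious difference between arms is:

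- unadjusted follow-up: c
- change from baseline: |c − b|, SE = √(4(1 − ρ)/20)
- baseline-adjusted: |c − ρb|, SE = √(2(1 − ρ²)/20)

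The false-positive rate is P(|Z + bias/SE| > 1.96).

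*Shift present at D0 only (c = 0):*

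| b | ρ | Adjusted: bias (SE) | False-positive rate | Change: bias (SE) | False-positive rate |
|---|---|---|---|---|---|
| 0.1 | 0.3 | 0.03 (0.30) | 5.1% | 0.1 (0.37) | 5.8% |
| 0.2 | 0.5 | 0.10 (0.27) | 6.5% | 0.2 (0.32) | 9.7% |
| 0.5 | 0.7 | 0.35 (0.23) | 34% | 0.5 (0.24) | 53% |

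The unadjusted comparison has no bias from this source.

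*Shift that persists unchanged (c = b):* the change score has bias 0. The adjusted estimate has bias (1 − ρ)b, which runs from 0.3 × 0.1 = 0.03 to 0.7 × 0.5 = 0.35 SD. The unadjusted comparison carries the full b.

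**3. Cost of setting the baseline aside**

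Without adjustment, the detectable difference at 80% power is (1.96 + 0.84) × √(2/20) = 0.89 SD. At ρ of 0.5 to 0.7, a clean baseline would remove ρ² = 0.25 to 0.49 of the outcome variance.

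**4. The 4-month set**

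If news of recurrence moves a score by g SD (assumed 0.5 to 1.0), the resulting difference between arms is g × (p_control − p_ProCel).

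- With equal recurrence of 20% or 30%, the difference is 0. The added variance is g²p(1 − p), from 0.25 × 0.16 = 0.04 to 1 × 0.21 = 0.21 SD².
- With 30% against 10%, the difference is 0.1 to 0.2 SD, and it arises through recurrence.

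**The case against.** Several objections carry weight.

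- **Knowledge of the arm at D0 is not stated.** Completing the forms on D0 before allocation fits every section of the Protocol, and the text calls this set a baseline. This stands. The defect is that the order is left open in a schedule where the wrong order is the more natural one.
- **The D0/D1 conflict is part of the problem.** This also stands. The two must be reconciled before the order can be settled, though neither numbering secures a pre-allocation score.
- **Section 3.2.3 names no baseline-adjusted or change analysis of the scales.** This is correct. The choice may lie in a statistical analysis plan that is not shown, and an unadjusted follow-up comparison would be untouched. But the forms are collected at baseline for some use, and their timing can be fixed only before collection.
- **The larger error rates are the corner of one scenario.** They need a shift of 0.5 SD that has vanished by follow-up. Participants stay unblinded, so the shift may persist. A post-allocation baseline would then partly or wholly cancel it, while a pre-randomisation baseline would leave it in the comparison. This stands. The fix restores a true baseline and does not remove open-label reporting bias.
- **Most of the instruments look back.** The Perceived Stress Scale covers the last month, most QLQ-C30 items the past week, and many MCQ-28 items four weeks or the time since diagnosis. Much of those periods may predate allocation. This limits the concern mainly to the State Optimism Measure.

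A reader might also infer from the 4-month timing that the comparison reflects imaging news rather than ProCel. The Protocol does not support that. Review and imaging apply to both arms on the same schedule, so the news mainly adds noise. Any difference that arises through recurrence is part of the effect of assignment. Nor does the Protocol give any reason to change the D20 set.

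**Conclusion.** The point holds as a minor one. The schedule fixes the first questionnaires on the day on which it also starts treatment, in a trial where participants know their arm, and does not require them to precede randomisation. A post-allocation baseline is the probable result. That rests on inference, because randomisation has no study day and the start of drug is given as both D0 and D1.

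The possible bias applies only to change-from-baseline or baseline-adjusted comparisons for a secondary endpoint of a 40-participant pilot. The Protocol gives no basis for its size. The ranges of 0.03 to 0.35 SD (adjusted) and 0.1 to 0.5 SD (change) depend on an assumed shift of 0.1 to 0.5 SD that does not last to follow-up, and on assumed correlations of 0.3 to 0.7. They show what could happen and do not predict it. It would go too far to conclude that the questionnaire results are invalid or that the false-positive rate is known to be inflated.

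**What to change.** Change the timing in the first questionnaire row to after consent and before randomisation, on or before D0, and record the completion date. Under section 5.3 consent is given at the second clinic appointment and the cardiologist's review comes before randomisation, so there is a natural slot and no new visit or form is needed. The cost is one table cell and one recorded date. The downside is a baseline taken some days earlier. N is unchanged.

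State where randomisation falls in the schedule, and reconcile D0 and D1 as the start of ProCel between the table and the dosing text, so that the order can be checked.

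Optionally, have the 4-month forms completed before that visit's results are discussed. This serves precision and interpretation only. It will not help where a participant has already learned of a recurrence.

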**Baseline**

**bloods, inflammatory**

**and immune markers**

**within 4 weeks of**

**study commencement**

**Randomised 1:1**

Treatment arm: 20 day ProCel regimen for 5d preoperatively, operative day and 14d postoperatively

Control arm

Surgical excision of metastasis as per clinical practice with routine paraffin sections and 1mm^2^ cores x 2 from each sample for tissue microarray analysis for proliferative, immune and inflammatory markers

Bloods for inflammatory and immune markers 2 weeks postoperatively

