### **5.2. Investigation Plan**

Eligible participants randomised to ProCel will receive propranolol in combination with celecoxib for five days preoperatively, day of surgery and for 14 days postoperatively:

The study drugs will be sourced through the RPA Investigational Drugs Unit pharmacy.

**Celecoxib:** 200 mg/bd D1-20 [equivalent to etodolac 400bd]; participants will be provided with two bottles of 30 x 200mg tabs

**Propranolol:** participants will be provided with two bottles of 100 x 10mg tablets

D1-D2 Propranolol 20mg bd

D3-D5 Propranolol 40mg bd

D6 ***SURGERY***  Propranolol 60mg bd

(baseline blood pressure, heart rate recorded preoperatively on day of surgery; anaesthetist review preoperatively on day of surgery as per standard clinical care)

D7-D13 (D13=7 days postop)Propranolol 40mg bd

D14-D20 (D20=14d postop) Propranolol 20mg bd

(wound review and tablet adherence assessment at D20)

Participants will be provided with a pulse oximeter to record their heart rate each day. If heart rate is <60 beats per minute, participants are advised to continue the current dose, not increase the dose, and to notify the research team. If participants experience dizziness or shortness of breath, they are advised to stop taking propranolol, and to notify the research team. If the treating anaesthetist determines heart rate and blood pressure are too low for safe anaesthesia, surgery will not proceed.

Excised tumour will be used for routine histopathology, as well as for marker studies using imaging mass cytometry to assess tumour immunology and proliferation. This technique enables assessment of approximately 40 immune, proliferation and angiogenesis and apoptosis markers in each 1mm tissue core. Markers may include, but need not be limited to, markers such as B2M-c, CD11c, CD14, CD141, CD163, CD16a-c, CD1c-c, CD20, CD27-c, CD31, CD34, CD38, CD39, CD3e, CD4, CD45, CD45RO, CD68, CD8, CollagenIV, FOXP3, GZMB, HLA-A, HLA-DR, HLA-E, ICOS, IDO1, Ki-67, LAG3, MITF-c, MLANA-c, PD-1, PD-L1, PMEL-c, S100B-c, SMA, SOX10-c, TBET-c, TCF7-c, TIM3-c, Vimentin and VISTA.

Routine blood samples will be taken 5-28 days preoperatively (before the start of ProCel treatment) for routine testing (full blood count, electrolytes, creatinine, liver function tests and any other bloods that are clinically relevant for individual participants, eg coagulation studies) and also for blood inflammatory and immune markers.

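### The D0 start label and two blood-sampling windows in the schedule disagree with the rest of the protocol, and baseline questionnaires need not precede randomisation

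*Protocol*

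**What the plan says.** **Start of treatment.** The schedule table under Protocol Compliance puts ProCel at D0 with the note "Commenced 5d preoperatively: (D0"). The next row reads "Excision specimens obtained after 5d of ProCel regimen and controls (D6 = day of surgery"). The dose list in Section 5.2 begins with "D1-D2 Propranolol 20mg bd" and ends with "D14-D20 (D20=14d postop) Propranolol 20mg bd"; celecoxib also runs from D1 to D20. The Summary describes a "20 day ProCel regimen for 5d preoperatively, operative day and 14d postoperatively". Adherence is judged from patient reports and "counting of unused tablets".

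**Postoperative blood.** Section 3.2.2 and the schedule table give D20 to D27. The later text of Section 5.2 gives D19 to D26 and equates D20 with postoperative day 15.

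**Baseline blood.** Section 5.2 and Appendix 2 place it between 5 and 28 days before surgery and before ProCel starts. The schedule table allows D0 or up to four weeks earlier. The Summary flow chart says "within 4 weeks of" study commencement.

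**Baseline questionnaires.** The schedule table fixes these at D0 and leaves the notes cell empty. The Quality of Life Questionnaires paragraph says only that they are completed at baseline. Consent, eligibility, history and concomitant medications may be done at or before D0, and the ECG row adds "Baseline; for cardiologist review prior to randomisation". Randomisation has no row and no study day. The Summary states that participants and treating clinicians are not blinded.

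**The concern.** A schedule table is what site staff work from. If its day labels disagree with the dose list and the endpoint definitions, the start day, the adherence count and the in-window status of a sample depend on which page is open. A D19 or D27 sample is valid or a deviation for endpoint 3.2.2 according to the section read. The same holds for a baseline sample drawn 29 to 34 days before surgery.

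The questionnaires raise a different issue. As printed, they share D0 with the start of treatment. Unlike the bloods, they carry no pre-treatment condition, and unlike the ECG review, they are not tied to randomisation. A participant who already knows the allocation may report stress, optimism or quality of life differently. A baseline collected that way cannot be repaired at analysis. The State Optimism Measure is the most exposed because it asks about the present moment. The Perceived Stress Scale asks about the last month and is less so.

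**Working it through.** Surgery is D6 in both the dose list and the schedule table, so all days are counted from there.

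**Regimen length (the plan's own figure).**
- Summary: 5 + 1 + 14 = 20 days.
- Dose list: D1 to D5 (5 days), D6, and D7 to D20 (14 days) = 20 days. The stated figure reproduces with a D1 start.
- Five days before D6: 6 − 5 = D1. D0 is 6 days before surgery.
- A D0 start would give 6 preoperative days and 21 days in all, contrary to the table's own note that specimens follow 5 days of treatment.

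**Tablet count.**
- Celecoxib is taken twice daily: 2 × 20 = 40 tablets of the 2 × 30 = 60 supplied.
- Counting D0 to D20: 2 × 21 = 42 expected. A fully adherent patient would score 40/42 = 95%.
- The protocol sets no adherence threshold, so this figure triggers no action.

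**Postoperative blood.**
- D20 to D27 is 14 to 21 days after surgery, matching the table's gloss of two to three weeks.
- D19 to D26 is 13 to 20 days after surgery.
- The two windows together cover 9 days (D19 to D27). Seven are shared (D20 to D26) and two are disputed (D19 and D27).
- By the dose list's count, 15 days after surgery is 6 + 15 = D21, not D20.

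**Baseline blood.**
- Section 5.2 and Appendix 2: 28 to 5 days before surgery = D−22 to D1.
- Schedule table: D−28 to D0 = 34 to 6 days before surgery.
- Summary: the outer limit is 34 days before surgery if study commencement is D0, or 33 if it is D1. The protocol does not say which, so both are shown.
- The outer limits differ by 33 − 28 = 5 to 34 − 28 = 6 days.
- The inner limit in Section 5.2 and Appendix 2 falls on D1, the first dosing day. Their stated condition that blood precedes ProCel keeps the sample pre-dose.

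**Questionnaires.** No arithmetic applies. Allocation must be known before study drug can be supplied for a D1 first dose, so a questionnaire completed on D0 can fall either side of randomisation. Correcting the start label to D1 would put D0 before the first dose, but would not put it before allocation.

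**The case against.** The dose list settles the start day. It names D1 for both drugs and assigns no dose to D0, so staff following it would not start early. This stands. A reader might infer that the protocol builds in a six-day preoperative course, but the dose list, the 20-day total and the table's own specimen note all rule that out.

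Every section gives D20 as the target day for postoperative blood, and day 15 fits if the day of surgery is counted as day 1. This also stands; only the edges of the permitted range conflict.

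For baseline blood, a reader might infer that a sample could be taken after dosing begins. The pre-ProCel condition in Section 5.2 and Appendix 2 prevents that. Only the anchor and the outer limit are in dispute, and the documents show no consequence for a marker drawn at day 34 rather than day 28.

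The strongest objection concerns the questionnaires. No section places them after randomisation, and completing them on D0 before allocation is compatible with the text. Section 3.2.3 names scores at D14 and 4 months. Its mention of baseline qualifies the blood and tumour markers, so it does not define change from baseline in the questionnaire scores. Hence it cannot be said that the baseline will be contaminated, or that the endpoint as worded depends on it. What remains is that the timing permits it, and that any baseline-adjusted or change analysis would inherit the problem.

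**Conclusion.** The concern holds as a minor one. The start label is wrong by one day. Two of nine postoperative sampling days are disputed, and the outer limit for baseline blood differs by 5 to 6 days. These errors apply to both arms, so their effect is inconsistent handling of samples and deviations. A reader might take them as a source of bias between arms, but nothing in the protocol shows that, and the primary tumour endpoint is not touched.

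The questionnaire timing is the only part that could affect a between-arm comparison. It does so only if some participants answer after learning their allocation and the analysis uses the baseline score. Neither is established: the share affected is unknown because randomisation has no study day, and the analysis is not stated in this document. The exposure is confined to self-reported secondary outcomes, chiefly the State Optimism Measure.

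**What to change.** 1. In the schedule table, change the ProCel row to D1.
2. In the text of Section 5.2, give postoperative blood as D14 postoperatively (= D20), range D20 to D27, matching Section 3.2.2 and the table.
3. Use one baseline-blood window in the Summary, Section 5.2, the schedule table and Appendix 2. For example: D0 or up to 28 days before D0, and always before the first dose. This extends the outer limit in Section 5.2 and Appendix 2 from 28 to 34 days before surgery. If the team prefers the shorter limit, the surgery anchor can be kept, provided all four places agree.
4. Change the baseline questionnaire row to at or before D0, after consent and before randomisation.

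The cost is wording changes. Some questionnaires would be completed slightly earlier than D0; no sample, visit or participant is added.

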3.2.1 Safety and tolerability (adverse events)

3.2.2 Serum inflammatory markers at D14 postoperatively (D20-D27)

3.2.3 Quality of Life, perceived stress and state (modifiable) optimism at D14 and at 4 months postoperatively, and correlation with baseline and postoperative blood and tumour inflammatory and immune markers.

3.2.4 Evidence of disease recurrence/progression at 4 months postoperatively in the 2 arms (based on staging investigations performed as part of routine clinical care. This usually includes PET-CT and brain imaging 3-4 monthly postoperatively and this data will be available for patients in both arms of the study.

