# **6. SAFETY**

Adverse events will be recorded at each visit and graded using the NCI Common Terminology Criteria for Adverse Events Version 4.0 (CTCAE).

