### **6.2. Adverse Events**

6.2.1 Any death (i.e. grade 5 event) which occurs while a patient is receiving protocol treatment or occurring within 30 days of stopping study agent must be reported on a Serious Adverse Event Report (SAE) form and sent to the PI within 10 working days of the event. This form must be signed by the responsible investigator.

6.2.2 All grade 4 unexpected reactions occurring within 30 days of stopping study treatment must be reported on an SAE form to the PI within 10 working days of the event. This form must be signed by the responsible investigator.

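### The adverse-event window and the Section 6.2 reporting triggers run on ProCel exposure, so controls have no stated end of AE collection and no clearly assigned contact between D20 and the 4-month review

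*Protocol*

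**What the plan says.** **Provisions tied to drug exposure**

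- Section 5.2, schedule table under Protocol Compliance, adverse-event row. The timing is "During and for 30 days after ProCel regimen". The assessment days are "D6 (day of surgery), D20 (postop followup), D45 (30 days after ceasing medication".
- Section 6.2.1. A death goes on an SAE form to the PI within 10 working days if it is one "which occurs while a patient is receiving protocol treatment or occurring within 30 days of stopping study agent".
- Section 6.2.2 sets the same form and deadline for "All grade 4 unexpected reactions occurring within 30 days of stopping study treatment".

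**Provisions that apply to both arms**

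- Section 6: "Adverse events will be recorded at each visit and graded using the NCI Common Terminology Criteria for Adverse Events Version 4.0 (CTCAE".
- Section 6.1: any SAE arising while a person takes part in the study is reported to the PI, by the route set out in the text that follows, and the ethics committee is told.
- The tumour-assessment row of the same table puts controls on the study-day clock: "Excision specimens obtained after 5d of ProCel regimen and controls (D6 = day of surgery". The D20 blood and questionnaire rows are not limited by arm.
- Section 10: the DSMB reviews serious and other adverse events and meets if an SAE occurs, with no restriction by arm.

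**Objective.** Section 3.2 asks for the effect of the regimen on a list of outcomes, the first of which (3.2.1) is safety and tolerability, measured by adverse events. The design is 1:1 randomised and open-label, with N = 40.

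**The concern.** All participants have surgery inside the observation period, so wound, bleeding and cardiovascular events can occur in either arm without any drug effect. The regimen's effect on adverse events can be separated from operative morbidity only if both arms are observed over the same period with the same contacts.

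The one AE window that the protocol states opens and closes with a regimen that controls never take. Its last contact is defined by an act, stopping medication, that controls never perform. A site following the table would make a safety contact after D20 for ProCel participants and could reasonably make none for controls. Clinicians and participants know the allocation, so nothing in the conduct of the trial would even out that difference.

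This is about data collection. A statistical analysis plan cannot recover control events that nobody asked about.

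**Working it through.** **1. Which safety provisions reach a control participant?**

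| Provision | Anchor | Reaches controls? |
| --- | --- | --- |
| Table, AE window | ProCel regimen | No period defined |
| 6.2.1, deaths | Protocol treatment, study agent | Not as worded |
| 6.2.2, grade 4 unexpected reactions | Study treatment | Not as worded |
| 6, AE recording | Each visit | Yes |
| 6.1, SAE reporting | Participation | Yes, but by a route set out in 6.2 |

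Three of the five are exposure-anchored and two are arm-neutral. Of the three listed AE assessment days, D6 and D20 apply to controls and D45 is labelled by drug cessation. The next scheduled contact that does not depend on drug is the 4-month review (range 3 to 5 months).

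**2. Can the plan's own end day be reproduced?** The table gives D45 as 30 days after the last dose. Section 5.2 puts the last dose at D20, 14 days after surgery on D6.

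- Last dose D20: 20 + 30 = D50.
- Start on D0, as the table's treatment row has it, with 20 dosing days: last dose D19, and 19 + 30 = D49.
- Postoperative clock with surgery as day 1: D20 is day 20 − 6 + 1 = 15, and 15 + 30 = postoperative day 45. That is study D50 (45 + 6 − 1).
- Postoperative clock with surgery as day 0: 14 + 30 = day 44.

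The figure 45 appears only as a postoperative day with surgery counted as day 1. D6 and D20 in the same cell are study days. Read as a study day, D45 is 45 − 20 = 25 days after the last dose, 5 days short of 30. The window also moves with the actual stop date: a participant who stopped on D10 would close at D40. So controls cannot simply inherit the treated arm's end date, because that date is not fixed.

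**3. Size of the ascertainment effect.** Let p be the background risk of at least one AE over the full window, equal in both arms (no drug effect). Let f be the share of those participants whose only events come after D20. If ProCel is followed throughout and controls only to D20:

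- observed ProCel risk = p
- observed control risk = p(1 − f)
- apparent risk ratio = p / [p(1 − f)] = 1/(1 − f)

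The result does not depend on p. The protocol gives no value for f, so a range is shown:

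| f (assumed) | Ratio, no later capture in controls | Ratio, half of late events captured later |
| --- | --- | --- |
| 10% | 1/0.90 = 1.11 | 1/0.95 = 1.05 |
| 25% | 1/0.75 = 1.33 | 1/0.875 = 1.14 |
| 50% | 1/0.50 = 2.0 | 1/0.75 = 1.33 |

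The last column replaces f by f × (1 − 0.5), for the case where the 4-month review recovers half of the late control events.

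In counts, with 40/2 = 20 per arm and an assumed p of 20% to 40%, ProCel shows 4 to 8 participants with an event. Controls show 3 to 6 at f = 25%, and 2 to 4 at f = 50%, with no later capture.

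**The case against.** The strongest reply is that the arm-neutral text already covers controls. A reader might infer from the exposure wording that controls have no safety collection at all, that a control's death need not be reported, or that serious control events would not reach the DSMB. The documents do not support any of these:

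- Section 6 records AEs at each visit without regard to arm, and D6 and D20 are control time points.
- Section 6.1 makes participation the trigger for SAE reporting, and controls participate.
- Section 10 does not limit DSMB review or meetings by arm.
- Section 6.2.2 concerns unexpected reactions, which are naturally tied to exposure. It is an expedited-reporting rule and does not define which AEs are collected.

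Two further points count against a severe reading. The Summary words the safety objective as safety of the regimen, without the comparison with controls that it uses for blood markers. A doubling of apparent risk needs half of the background events to fall after D20, and none of those to surface at the 4-month review.

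All of this stands, and it narrows the point without removing it. Recording at each visit gives neither a common last contact nor an end of collection. Section 6.1 refers the reader to 6.2 for the manner of reporting, and what 6.2 offers is worded for people on drug, so the form and the 10-working-day deadline for a control death are left to interpretation. Whatever the Summary says, Section 3.2 asks for the regimen's effect, and that needs like-for-like observation in both arms.

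**Conclusion.** The point holds in a limited form. The exposure-anchored provisions (table row, 6.2.1, 6.2.2) and the arm-neutral ones (6, 6.1) do not agree. As a result, all 20 controls lack a stated end of AE collection and a clearly assigned contact between D20 and the 4-month review, and the reporting route for a control death is unclear.

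If the table is followed literally, the bias runs against ProCel. Its size is unknown: an apparent risk ratio of 1.11 to 2.0 for f from 10% to 50% with no later capture, and smaller if the 4-month review recovers some events. These ratios rest on an assumed f, equal background risk in both arms, and sites making the D45 contact only in the ProCel arm. If sites already make it in both arms, there is no bias and the fault is in the wording alone.

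Separately, D45 and its label in the same row disagree by 5 days on the study-day clock (4 if dosing starts on D0).

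**What to change.** 1. State one AE/SAE collection window for both arms, from randomisation to a fixed day counted from surgery. Use the planned surgery date if the operation does not go ahead.
2. List the same AE contacts for both arms in the schedule table. A phone call is enough for controls at the last one.
3. In 6.2.1, use that window for deaths. Say that SAEs in controls follow the same form and deadline, so that 6.2 agrees with 6.1. Section 6.2.2 can remain a rule about reactions to study drug.
4. State that the DSMB receives AEs and SAEs by arm.
5. In the same edit, reconcile D45 with its label. If 30 days after the scheduled D20 last dose is meant, the window ends 14 + 30 = 44 days after surgery, which is study D50. If D45 is meant, it ends 45 − 6 = 39 days after surgery and the label must change.

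The cost is a protocol wording change and about 20 extra phone contacts. Sample size, randomisation and the primary endpoint are unaffected.
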